# Effectiveness, safety, and economic evaluation of topical application of a herbal ointment, *Jaungo*, for radiation dermatitis after breast conserving surgery in patients with breast cancer (GREEN study)

**DOI:** 10.1097/MD.0000000000015174

**Published:** 2019-04-12

**Keywords:** breast neoplasms, herbal medicine, ointments, radiodermatitis, randomized controlled trial, traditional Korean medicine

## Abstract

**Introduction::**

This is a prospective, open-label, parallel-group, randomized controlled trial that evaluates the effectiveness and safety of adjuvant application of *Jaungo* (JUG) for radiation-induced dermatitis (RD) in breast cancer patients undergoing radiation therapy, in comparison with general supportive care (GSC).

**Methods/design::**

Eighty female patients, who have been diagnosed with unilateral breast cancer, will be allocated to either the JUG or GSC group with an allocation ratio of 1:1 after breast conservation surgery, in the Kyung Hee University Korean Medicine Hospital, Seoul, Republic of Korea. Both the groups will be subjected to GSC, but only the JUG group participants will apply adjuvant JUG ointment on the irradiated skin for 6 weeks, twice a day. The primary outcome of this study is the assessment of incidence rate of RD using the Radiation Therapy Oncology Group (RTOG) for toxicity gradation of 2 or more. Maximum pain level, quality of life, adverse reactions, and pharmacoeconomic evaluations will also be included.

**Discussion::**

The primary outcome will be statistically compared using the logrank test after estimating the survival curve using the Kaplan–Meier method. Continuous variables will be tested using independent *t* test or Mann–Whitney *U* test. The adverse events will be evaluated with Chi-square or Fisher exact test. All the data will be analyzed at a significance level of 0.05 (two-sided) with R software (The R Foundation).

**Trial registration::**

CRIS (Clinical Research Information Service), KCT0003506, 14 February 2019.

## Introduction

1

Almost 90% of the patients undergoing radiotherapy for breast cancer have been reported to develop radiation-induced dermatitis (RD).^[1]^ The complaints vary from erythema to moist or dry desquamation^[2]^ that results in significant discomfort, restriction of daily activities, and even cessation of necessary radiotherapy.^[1]^ There have been several studies reporting prevention or treatment of RD with the external application of skin products including aloe vera gel,^[3]^ anionic phospholipid-based cream,^[4]^ wound healing ointment,^[5]^ corticosteroid therapy,^[6]^ or hyaluronic acid-based formulation.^[7]^ Breast intensity-modulated radiation therapy (RT) was also proposed to reduce the occurrence of moist desquamation in acute RD.^[8]^ Additionally, washing skin with water and soap during radiotherapy for breast cancer could be helpful because it could remove skin microbes that cause skin inflammation.^[9]^ However, there is no standard therapy or consensus on the optimal management of RD in the breast cancer patients till date.^[10]^

*Jaungo* (JUG) is a herbal ointment consisting of *Angelica gigas radix* and *Lithospermum radix*, which are the usual ingredients prescribed for various skin disorders in clinical practice of traditional Korean medicine (TKM), such as burns, eczema, psoriasis, or frostbite.^[11]^ There have been several in vivo and in vitro studies demonstrating the efficacy of JUG in dermatopathy. JUG has known to significantly promote wound healing on both the sterilized and infected wounds of Sprague-Dawley rats.^[12,13]^ Shikonin, the active compound of *Lithospermum radix*, enhances cell migration of intestinal epithelial cells through a mechanism that involves transforming growth factor-β induction, thus implying that JUG could help to heal intestinal injuries.^[14]^ Shikonin also significantly attenuates the inflammatory response in cellular models exposed to lipopolysaccharide.^[15]^ Furthermore, decursinol angelate, a coumarin compound of *Angelica gigas radix*, showed anti-inflammatory activities that inhibited the expression of pro-inflammatory cytokines and matrix metalloproteinase-9.^[16,17]^

There have also been a few clinical trials that explored the effectiveness and safety of JUG in RD. Patients undergoing RT for brain tumors showed favorable improvement or meaningful prevention of scalp dermatitis after topical application of JUG.^[18,19]^ A pilot study randomly allocated 30 breast cancer patients and evaluated the incidence of RD with Radiation Therapy Oncology Group (RTOG) toxicity of grade 2 or more, resulting in lowering of the RD incidence in the JUG treatment group with no safety issues, as compared to the general supportive care (GSC) group.^[20]^

This study protocol is primarily aimed at showing the effectiveness and safety of the adjuvant application of JUG for RD in breast cancer patients undergoing RT, as compared to GSC, along with its pharmacoeconomic evaluation.

## Methods/design

2

This study protocol adheres to Standard Protocol Items: Recommendations for Interventional Trials (SPIRIT) 2013 statement,^[21]^ and Standard Protocol Items for Clinical Trials with Traditional Chinese Medicine 2018: Recommendations, Explanation and Elaboration (SPIRIT-TCM Extension 2018).^[22]^

### Objectives and hypothesis

2.1

The primary objective of this study is to evaluate the effectiveness of adjuvant application of JUG on the irradiated skin of breast cancer patients undergoing RT after breast conserving surgery, with comparison of only GSC treatment. This will be assessed by the incidence rate of RD with RTOG toxicity grade of 2 or more. The secondary outcomes to be assessed and compared between the JUG and GSC arms include the time of initial RD occurrence, RD duration, maximum pain level, and quality of life (QoL). Additionally, the safety and pharmacoeconomic variables will be evaluated for JUG application in breast cancer patients.

### Study design and setting

2.2

This is a prospective, open-label, parallel-group, randomized controlled trial. This study will enroll 80 female patients, who have been diagnosed with unilateral breast cancer confirmed by biopsy and supposed to undergo RT of 50 to 64 Gy dose after breast conserving surgery. They will be allocated to either the JUG or GSC group with an allocation ratio of 1:1. Both groups will be subjected to GSC, but only the JUG group will apply the adjuvant JUG ointment on the irradiated skin for 6 weeks, twice a day. Eligible participants will be enrolled from the in-patients or out-patients of the Kyung Hee University Korean Medicine Hospital, Seoul, Republic of Korea. Study advertisements will be posted on webpages and notice boards to promote subject enrollments.

The study flow is depicted in Figure 1.

**Figure 1 F1:**
[figure not shown]
Study flow. ^∗^JUG treatment will be applied only for the intervention group (a dotted line). ECOG = Eastern Cooperative Oncology Group, EQ-5D-5L = EuroQoL Five Dimensions questionnaire 5-Level, IPCQ = iMTA Productivity Cost Questionnaire, JUG = *Jaungo*, RTOG = Radiation Therapy Oncology Group, VAS = Visual Analogue Scale.

### Eligibility criteria

2.3

Female patients aged 19 to 80 years old and diagnosed with unilateral breast cancer based on biopsy are eligible for participation in this study. The other inclusion criteria include: RT with a total dose of 50 to 64 Gy without bolus, after breast conserving surgery; and Eastern Cooperative Oncology Group performance status of 1 grade or less. All the eligible participants have to provide voluntarily signed written/informed consent forms after understanding the trial details.

The exclusion criteria are: inflammatory breast cancer; skin invasion or distant metastasis of tumor; concurrent chemotherapy with RT, except for herceptin and hormone therapy; untreated wounds, severe/extensive burn, dampness, erosion, or suppuration on breast skin; fever; history of prior RT to the chest wall; history of connective tissue disorders; history of heart diseases such as arrhythmia, uncontrolled hypertension, severe mental disorders (dementia, drug addiction, etc.) demanding intensive treatment, or paralysis; or history of hypersensitivity reaction to the study drug or it is ingredients. Participants who are involved in other trials within that month or disagree with contraception during the study period will also be considered ineligible.

### Randomization, allocation concealment, and blinding

2.4

An independent statistician will generate random sequence numbers using the R version 3.5.2 (The R Foundation) with blockrand package version 1.3. Eligible participants will be randomly allocated to either the JUG or GSC group in a ratio of 1:1, and the allocation will be concealed using the sealed envelope method. The sealed envelopes will include random numbers and allocated groups, and the investigators will open the envelopes to assign the participants to particular groups after completing the screening process. Since JUG will be prescribed only to participants of the JUG treatment group, this trial is an open-label study.

### *Jaungo* treatment

2.5

JUG ointment (product name: *Hanpoong Jaungo*, pharmaceutical company: *Hanpoong Pharm*. Co Ltd, Seoul, Republic of Korea) consists of two active herbs, *Angelicae gigantis radix* (*Angelica gigas Nakai*, family Umbelliferae) 60.6 mg/g and *Lithospermi radix* (*Angelica gigas Nakai*, family Boraginaceae) 72.7 mg/g, which are standardized based on the Korean Pharmacopoeia. The ointment also contains sesame seed oil, bees wax, and swine oil as carriers. JUG is packaged as a 15 g pumping bottle. The participants assigned to the JUG group will be provided with two bottles of JUG on the 2nd (day 0) and 5th visit (day 21), respectively. The JUG has to be applied on the irradiated parts of the breast skin by themselves, twice a day (every morning and evening) for 42 days, which is the period of RT for breast cancer. Patients are supposed to record drug use diary and return the bottles on the next visit for adherence evaluation.

### Radiation therapy and general supportive care

2.6

All the patients will undergo RT at a dose of 2 Gy/day without bolus by a medical specialist of radiation oncology. The whole breast irradiation with photon beam will be implemented for 5 weeks (5 times a week) and a boost irradiation with photon or electron beam will be added for 1 week (5–7 times a week), if necessary. Additionally, the regional lymph node irradiation could be included, covering axilla level II/III for irradiation.

Participants allocated to the treatment or control group will be instructed to wash the irradiated skin with clean water or wet towels, and wipe the skin with dry towels in order to keep the irradiated skin clean and dry. Furthermore, any lotion or cream can be applied to the breast skin. This GSC regimen is based on a preceding study^[9]^ and a pilot trial.^[20]^

Any other type of preventive or treatment management of RD is prohibited during study participation.

### Outcomes

2.7

Data will be collected and recorded in case report forms. An independent monitor will regularly visit the study site for source data verification, investigator product management, protocol deviation check, and safety issue monitoring.

### RTOG toxicity scale

2.8

The primary outcome of this study is the incidence rate of RD of RTOG toxicity grade 2 or more. A radiation oncologist will assess the irradiated skin of the patients at every visit, based on the Cooperative Group Common Toxicity Criteria for skin suggested by the RTOG Foundation (https://www.rtog.org). The toxicity is graded at 6-levels: 0 for none or no change, 1 for scattered macular or papular eruption or erythema that is asymptomatic, 2 for scattered macular or papular eruption or erythema with pruritis or other associated symptoms, 3 for generalized symptomatic macular, papular, or vesicular eruption, and 4 for exfoliative dermatitis or ulcerating dermatitis.

Furthermore, the time of RD onset and RD duration with grade 2 or more of RTOG toxicity will be evaluated.

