### Sample size

2.13

In the pilot study, occurrence rate of RD with RTOG toxicity grade 2 or more was 46.7% and 78.6% in the JUG and GSC groups, respectively.^[20]^ The null hypothesis is that *S*_*JUG*_ (t) = *S*_*GSC*_ (t), where *S* denotes the probability that RD does not occur during RT of breast cancer patients (*S*_*JUG*_ (t) = 53.3%, *S*_*GSC*_ = 21.4%). The sample size has been calculated as 36 per group (two-sided, α = 0.05 and 1-β = 0.8) with logrank test of PASS software version 14.0.11 (NCSS Statistical Software). With a 10% drop-out rate expected, we have decided to enroll 80 eligible participants (40 in each group).

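### No masking is stated for the radiation oncologist who grades the primary endpoint, although the stated reason for an open-label trial does not rule it out

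*Protocol article*

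**What the plan says.** The primary endpoint is defined in section 2.8 (RTOG toxicity scale): "The primary outcome of this study is the incidence rate of RD of RTOG toxicity grade 2 or more". The same section names the assessor: "A radiation oncologist will assess the irradiated skin of the patients at every visit".

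It also sets the event boundary. Just below the boundary is grade "1 for scattered macular or papular eruption or erythema that is asymptomatic". Just above it is grade "2 for scattered macular or papular eruption or erythema with pruritis or other associated symptoms".

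Section 2.4, whose heading includes blinding, has one sentence on the subject: "Since JUG will be prescribed only to participants of the JUG treatment group, this trial is an open-label study". Section 2.2 describes the comparison: "Both groups will be subjected to GSC, but only the JUG group will apply the adjuvant JUG ointment on the irradiated skin".

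No section says whether the grading oncologist knows the allocation. In section 2.7 an independent monitor checks source data, product handling, deviations and safety; skin grading is not among these tasks.

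**The concern.** The reason given for openness is about prescribing. It explains why participants and prescribers know the arm. It does not explain why the person who grades the skin should know it, and the plan contains nothing that would keep that person unaware.

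The endpoint is sensitive to such knowledge. Grades 1 and 2 share the same skin finding, and the event depends on whether symptoms are judged to be present. Section 2.11 lists local rash, redness and itching as expected adverse reactions, which overlaps with the features of grade 2. A grader who knows that a participant uses JUG has an alternative explanation for itchy erythema that does not exist in the GSC arm. The grade also determines two secondary outcomes, time of onset and duration of dermatitis.

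At stake is the interpretation of a positive result. If grading differed by arm, the logrank comparison could not separate that difference from a treatment effect.

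**Working it through.** **1. The plan's own figure.** Section 2.13 gives pilot rates: "occurrence rate of RD with RTOG toxicity grade 2 or more was 46.7% and 78.6% in the JUG and GSC groups, respectively". Event-free probabilities are therefore 0.533 and 0.214.

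- Hazard ratio = ln(0.533)/ln(0.214) = 0.629/1.542 = 0.408.
- Freedman events = (1.960 + 0.842)² × [(1 + 0.408)/(1 − 0.408)]² = 44.4, rounded up to 45.
- Mean event probability = (0.467 + 0.786)/2 = 0.6265, so 45/0.6265 = 71.8 patients, or 36 per arm.
- With 10% dropout, 36/0.9 = 40 per arm.

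This agrees with the plan: "The sample size has been calculated as 36 per group (two-sided, α = 0.05 and 1-β = 0.8) with logrank test". The sample size is not in question, and masked grading would not change it.

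**2. Illustration of differential grading.** The documents give no misgrading rate, so every value of m below is an assumption. Further assumptions are no true effect (the same true incidence p in both arms) and 40 per arm. The test is a two-sided two-proportion chi-square at 0.05 without continuity correction, with the rejection probability found by exact enumeration of all pairs of binomial outcomes.

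- Downgrading only: a share m of JUG events is graded below 2. Observed JUG = p(1 − m); observed GSC = p.
- Both directions: in addition, a share m of GSC non-events is graded 2 or more. Observed GSC = p + (1 − p)m.

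Example with p = 0.60 and m = 0.20: JUG = 0.60 × 0.80 = 0.48. GSC = 0.60 with downgrading only, or 0.60 + 0.40 × 0.20 = 0.68 with both.

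| Scenario | m = 0 | m = 10% | m = 15% | m = 20% |
|---|---|---|---|---|
| p = 60% (assumed), JUG downgraded only | 5% | 9% | 14% | 20% |
| p = 60% (assumed), both directions | 5% | 15% | 29% | 46% |
| p = 78.6% (GSC rate, section 2.13), JUG downgraded only | 5% | 13% | 22% | 34% |

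**3. Check against the planned test.** Section 2.14 specifies a logrank test, and 36 per arm are expected after dropout. A logrank simulation used weekly assessments over 6 weeks, 36 per arm, p = 78.6%, downgrading of JUG events only, and 4,000 replicates. It rejected in about 5%, 13% and 35% of trials for m = 0, 10% and 20%. The chi-square approximation is therefore adequate here.

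**4. Benchmark.** To turn 78.6% into 46.7% by misgrading alone would need m = 1 − 0.467/0.786 = 41%. Reproducing the whole planned effect would thus take heavy misgrading; inflating the type I error takes much less.

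**The case against.** **Silence on masking does not prove that the grader knows the arm.** Sections 2.4 and 2.11 have investigators open the envelopes and assess adverse reactions, whereas section 2.8 has a radiation oncologist grade the skin. Some separation may exist, and the article condenses a longer protocol. This stands as a limit: a reader might infer that the grader is known to be unmasked, and the text does not say so. It does not remove the point. The section that covers blinding says only that the trial is open-label, without confining that to participants, and nothing in the plan as written keeps the grader unaware.

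**The bias need not favour JUG.** A reader might infer that it always would. No section establishes the direction of this assessor's errors; irritation from the ointment could even be counted as grade 2. A bias towards JUG is the more plausible direction, given the hope of significant results stated in the Discussion, but it is not certain.

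**The figures depend on the inputs.** This is correct. The 60% base rate and every m are assumed, and the two-direction scenario is the more severe at that rate. With 36 instead of 40 per arm, its values fall from 15%, 29% and 46% to about 13%, 25% and 40%. Not every choice inflates the result: at 78.6%, downgrading alone gives more than it does at 60%.

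**Masking the grader does not mask the symptom report.** This also stands. Participants know their arm and report the pruritus or other symptoms that define grade 2, so a masked grader is a partial remedy.

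**Masking may be hard to achieve.** Section 2.6 has a radiation oncology specialist deliver treatment over 5 to 6 weeks, and that may be the same person. JUG contains sesame oil, beeswax and swine oil, and nothing shows that the water washing described in section 2.6 removes them. Both are reasons to measure how well masking held, not to leave it out.

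**Conclusion.** The point holds as a design weakness that can be reduced at little cost. No masking is stated for the assessor of a symptom-dependent primary endpoint, and the reason given for an open-label trial does not prevent such masking. Confidence is high that the article contains no masking provision; whether the grader will in fact know the arm cannot be determined from it.

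The size is illustrative. With no true effect and 10% to 20% of JUG events downgraded, the nominal 5% error becomes 9% to 20% at an assumed 60% incidence, or 13% to 34% at the protocol's GSC rate. Equal upgrading of GSC non-events, at 60%, gives 15% to 46%. These figures show what modest differential grading could do in a trial of this size. A reader might take them as an estimate of the actual bias, or as evidence that the pilot difference arose from grading; the documents support neither reading.

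**What to change.** State in sections 2.4 and 2.8 that the trial is open to participants and prescribers, and that the radiation oncologist who grades the skin is kept unaware of allocation where feasible. In practice:

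- The grader does not open envelopes, dispense JUG, or see diaries or returned bottles.
- Participants are asked to clean the irradiated skin before grading and not to disclose their group.
- The RTOG grade goes on a form that does not show the allocation, and is completed before adverse-event and adherence questions are asked.
- The grader's guess of the arm is recorded at the last visit.

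This must be in place before grading starts, because grades given with knowledge of the arm cannot be masked afterwards. The cost is a change to visit flow and a separate form page. Sample size, endpoint and primary test stay as they are. No extra assessor is needed if the grading oncologist can be kept apart from these tasks.

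The downside is that masking may be imperfect, because residue may be visible or because the grader may also deliver radiotherapy; the recorded guess shows how far it held. The trial report should state that the symptoms defining grade 2 come from unmasked participants, so that some bias may remain.

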### Safety assessment

2.11

The adverse events will be evaluated and reported during the study. Local rash, rubescent, or itching are expected to be found from time to time. If an adverse reaction is found, then the investigators will assess the intensity/frequency of each episode and decide whether further treatments are necessary or not. Vital signs will be regularly checked to assess JUG safety.

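### The printed primary-outcome scale claims six levels but lists five, gives dry and moist desquamation no defined grade, and separates grade 1 from grade 2 by symptoms alone in an open-label trial

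*Protocol article*

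**What the plan says.** All references are to the protocol article.

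- **Section 2.8 (RTOG toxicity scale), endpoint:** "The primary outcome of this study is the incidence rate of RD of RTOG toxicity grade 2 or more". A radiation oncologist grades the irradiated skin at each visit. Time of onset and duration of RD use the same grade 2 threshold.
- **Section 2.8, lower grades:** the list opens with "The toxicity is graded at 6-levels: 0 for none or no change". The entry for the first abnormal grade reads "1 for scattered macular or papular eruption or erythema that is asymptomatic". The next step, where the primary event begins, is worded "2 for scattered macular or papular eruption or erythema with pruritis or other associated symptoms".
- **Section 2.8, upper grades:** the third grade is a widespread eruption with symptoms, vesicles included. The fourth, and last in the list, covers exfoliation or ulceration.
- **Introduction, on RD in these patients:** "The complaints vary from erythema to moist or dry desquamation".
- **Section 2.11 (Safety assessment):** "Local rash, rubescent, or itching are expected to be found from time to time".
- **Section 2.4 (Randomization, allocation concealment, and blinding):** the trial is open-label.
- **Section 2.13 (Sample size):** the pilot rates of grade 2 or more were 46.7% with Jaungo (JUG) and 78.6% with general supportive care (GSC). These give 36 per group, and 40 per group after dropout.

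**The concern.** Three features of the printed scale bear on what counts as a primary event.

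1. The stated number of levels does not match the list. Either a level has been lost or the count is wrong.
2. The protocol describes the disease by erythema and desquamation, but the grades are worded as eruption or erythema, with exfoliation or ulceration only at the top. Two assessors who see the same small area of peeling could grade it differently, and one choice could be an event while the other is not.
3. Grades 1 and 2 describe the same skin and differ only in whether there are symptoms. The assessor has to learn of itching or soreness from a patient who knows whether she is using the ointment. The local reactions that the safety section expects overlap with the grade 2 wording, and the article gives no rule for telling them from RD.

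At stake is the consistency and interpretation of the primary outcome, and of the onset and duration outcomes built on the same threshold. The planning rates also carry over only if the pilot graded skin in the same way.

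**Working it through.** **Level count.** Stated: 6. Listed: 0, 1, 2, 3, 4, which is 5. The two do not agree.

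**The plan's sample size.** Inputs from section 2.13: event-free proportions 0.533 (JUG) and 0.214 (GSC), two-sided alpha 0.05, power 0.80.

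- Hazard ratio = ln(0.533) / ln(0.214) = 0.408.
- Freedman events = (1.960 + 0.842)² × [(1 + 0.408) / (1 − 0.408)]² = 44.4, rounded up to 45.
- Mean event rate = (0.467 + 0.786) / 2 = 0.6265.
- Total = 45 / 0.6265 = 71.8, so 36 per group.
- With 10% dropout: 36 / 0.90 = 40 per group, 80 in all.

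The stated figures reproduce, so the sample-size arithmetic is not at fault. The question is whether the event behind those rates is the event printed in section 2.8.

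**The printed grades applied to five presentations.**

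| Presentation | Result under the printed wording | Primary event? |
|---|---|---|
| Scattered erythema, no symptoms | Grade 1 | No |
| The same erythema, with itching | Grade 2 | Yes |
| Erythema with peeling and soreness | Grade 2, through the other-symptoms clause | Yes |
| Limited dry or moist desquamation, no symptoms | No grade describes it: grade 1 names only eruption or erythema, grades 2 and 3 require symptoms, grade 4 is exfoliative or ulcerating | Undefined: no if scored 1, yes if scored 4 |
| Local rash or redness with itching, thought to be due to the ointment | Meets the grade 2 wording; no attribution rule is printed | Unclear |

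The first two rows show that symptoms alone can move a patient across the event threshold. The fourth shows the gap for desquamation. The fifth shows the overlap with the safety section.

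**Direction of bias.** Ointment reactions scored as grade 2 would add events in the JUG arm. Knowledge of allocation could lower symptom reports in that arm or raise them in the control arm. These effects oppose each other, and the documents give no rate for either, so the net effect cannot be calculated.

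**The case against.** The best defence is that a radiation oncologist assigns the grade, under a named external criterion, to an outcome defined as RD and not as any rash. Adverse reactions are already assessed separately under section 2.11. The pilot endpoint carries the same RTOG grade 2 label, so the documents show no mismatch with the planning rates. The level count may be a slip of wording that cannot itself move the grade 2 threshold.

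Much of this stands, and it rules out several stronger readings that a reader might infer:

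- **That itching defines grade 2.** It is sufficient but not necessary, because other associated symptoms also qualify. Symptomatic peeling with erythema therefore has a place.
- **That the protocol attributes rash and itching to JUG.** Section 2.11 does not name the cause. Its place in the safety section only suggests one.
- **That the scale is the wrong one, or differs from the pilot's.** Neither source is at hand, so this cannot be checked.
- **That the overlap costs a calculable amount of power.** If a share a of otherwise event-free JUG patients were scored grade 2 for a local reaction, the JUG rate would be 0.467 + a × 0.533. For a = 5, 10 or 15% that gives 49.4, 52.0 or 54.7%, and Freedman power at 36 per group would drop from 81% to 75, 68 or 61%. This does not hold. The 46.7% was itself observed in JUG-treated patients, so if the pilot used the printed scale such reactions are already counted. If it used another scale, both arms' rates under the printed one are unknown. No value of a appears in the documents, and the Introduction reports no safety issues in the pilot.

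The defence does not close the gap for limited desquamation. Nor does it alter the fact that an oncologist following this wording must rely on reported symptoms to separate grade 1 from grade 2. The article prints its grades in full, so these are defects in what is stated and not matters left to a longer document.

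**Conclusion.** The point holds as a defect in the definition of the primary event. The level count contradicts the list. Limited desquamation, especially without symptoms, has no defined grade although the protocol describes RD in those terms. The step from grade 1 to the primary event depends on symptoms reported without blinding, and reactions that the safety section expects could meet the same wording.

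No size is attached. The direction of bias is open and the sample size of 36 per group reproduces. The conclusion rests on the wording of sections 2.4, 2.8 and 2.11 and the Introduction. It does not assume that the pilot used a different scale.

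**What to change.** Before outcome data are seen:

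1. Reconcile the level count and grade wording in section 2.8 with the skin criteria actually used in the pilot, so that dry and moist desquamation each have a defined grade. If the pilot used the printed wording, keep it as the primary definition so that 46.7% and 78.6% still apply.
2. In either case, record observable signs (erythema, dry desquamation, moist desquamation) and symptoms as separate items on the case report form at the existing visits. If they are not recorded separately, they cannot be recovered later.
3. Flag suspected ointment reactions at the same visits.
4. Add one sensitivity analysis of the primary outcome that does not count events reaching grade 2 through symptoms alone.

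The cost is protocol and case-report-form wording and one extra analysis. The assessor and the visits do not change.
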